### Study population

#### Recruitment of participants

Preterm children hospitalized in the NICU of Zhongda Hospital Southeast University in line with the inclusion criteria are recruited as participants (Fig. 1).

Inclusion criteria:Gestational age <34 weeksChildren who can only be fed with formula due to their mothers’ sicknessChildren who are transferred to our hospital’s NICU immediately after birth, and have not started any enteral feeding before and during transfer, including water, glucose, formula, drugs, etc.Children whose cardiovascular, blood and nervous systems are stable when transferred to the NICU

Exclusion criteria:Occurrence of vomiting, abdominal distension, gastrointestinal hemorrhage or necrotizing enterocolitis (NEC) before preparation for enteral feedingOccurrence of cardiovascular, blood and nervous system instability (such as shock, disseminated intravascular coagulation (DIS), frequent convulsions, coma) before preparation for enteral feedingDiscovery of gastrointestinal malformations (esophageal atresia, esophageal fistula, biliary atresia, Hirschsprung’s disease, anal atresia, omphalocele, gastroschisis, congenital malrotation, etc.) before preparation for enteral feeding or after feedingChildren with congenital metabolic diseases and chromosomal disordersChildren with other serious congenital disorders (diaphragmatic hernia, cyanotic congenital heart disease, moderate to severe Pierre-Robin syndrome, etc.)Renal failure due to various causesChildren whose head computed tomography (CT) or B-mode head ultrasound prompts serious intracranial hemorrhage or hydrocephalusUse of drugs affecting gastric motility and gastric acid secretion (H_2_ receptor antagonists, proton pump inhibitors, gastrointestinal drugs)Occurrence of stage III necrotizing enterocolitis during hospital stay requiring transfer to a Children’s Hospital for observation and surgical treatmentReplacement for formula during hospital stayDeath during hospital stayEarly discharge against the criteria for discharge from the NICUChildren who suffer from diseases requiring parenteral nutrition or serious illness requiring intensive care unit (ICU) hospitalization or requiring hospitalization and surgery

Criteria for discharge from the NICU or transfer to direct rooming-in (DRI):Corrected gestational age ≥34 weeks, and weight ≥1500 gNo need for oxygen inhalation, stable vital signs, no apnea phenomenonAble to suck formula on their own, and coordinated sucking-swallowing-breathing actionHaving achieved full enteral feeding, daily milk volume ≥150 ml/kg, no need for any intravenous medicationAble to maintain normal body temperature at room temperature of 22–24 °CEach system is free from life-threatening pathological conditionsBirth weight has been restored, and weight begins to grow steadily

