#### Randomization and blinding

Randomization will be conducted by a researcher not involved in the recruitment and treatment of the participants. Concealed allocation will be performed using a set of random numbers placed in sealed opaque envelopes. The participants who meet the eligibility criteria will be divided into two groups by the physicians on duty via opening the envelopes. Reference to similar study literature is made for randomization [28, 31]. As extensively hydrolyzed milk protein formula and preterm children’s formula are greatly different in color and smell, physicians and nurses can easily distinguish these two formulae. Therefore, the study has chosen single-blinding, which means that only the participants and their guardians are unaware of the milk type.

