### Study design and outcomes

#### Outcomes

The first endpoint variable is the rate of food intolerance in preterm children. The second endpoint variables include (1) time to achieve full enteral nutrition; (2) time of parenteral nutrition; (3) time of NICU stay; (4) meconium drainage time; (5) daily spontaneous fecal discharge conditions; (6) growth and development conditions during the NICU stay and within 3 months after discharge, including daily weight growth rate, weekly body length growth rate and weekly head circumference growth rate; (7) different plasma parameter indicators before discharge from the NICU (total protein (TP), albumin, calcium (Ca), phosphorus (P), and alkaline phosphatase (ALP)). Other endpoint variables include the incidences of neonatal necrotizing enterocolitis, cholestasis, parenteral nutrition-associated cholestasis and congenital hypothyroidism (CH).

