### Stage I: NICU stay

Feeding timePreterm children without obvious high-risk factors are fed within 24 hours after birth.The feeding of preterm children with birth weight <1000 g, obvious history of asphyxia at birth (Apgar score ≤5), severe infection (sepsis, purulent meningitis, etc.), severe pneumonia or neonatal respiratory distress syndrome (NRDS) requiring intubation and mechanical ventilation should be postponed to 24–72 h after birth according to the situation.During the period when full enteral nutrition is not achieved, partial parenteral nutrition is given according to the daily amount of fluid and energy required by the children; when the children experience feeding intolerance and necrotizing enterocolitis and need to be fasting, complete parenteral nutrition is given; after the conditions are stable, the children gradually switch to enteral nutrition and are fed until discharge or transfer into DRI.Children in the two groups are fed with ordinary formula after discharge or transfer to DRI.Feeding methodsFor preterm children with a gestational age of <32 weeks, since their sucking-swallowing action is uncoordinated and respiratory function is not maturely developed, the children are given tube feeding (nasogastric tube or orogastric tube) using the intermittent infusion feeding method. Every time before feeding, the stomach contents are drawn to learn about gastric residual volume (GRV) and nature.Children suspected of suffering from gastroesophageal reflux or delayed gastric emptying are fed by adopting intermittent/continuous infusion feeding method with an infusion pump.Preterm children with a gestational age of 32–34 weeks are given direct bottle feeding.Children with weak sucking ability yet normal gastric emptying are given bottle feeding first, and then the remaining milk is given by tube feeding.Children with nasal continuous positive airway pressure (nCPAP) or intubation and mechanical ventilation are given tube feeding;During tube feeding or fasting period, the children are given non-nutritive sucking (NNS).Feeding milk volumeInitial feeding milk volume: according to birth weight, the children are fed from different initial milk volume once every two hours, as shown in Table 2.The milk volume begins to increase in the absence of feeding intolerance in 24-h observation, and the rates for milk increasing are shown in Table 2.

**Table 2 Tab2:** Initial feeding milk volume and increasing rate in the two groups of preterm children

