### Sample size justification

We calculate the sample size based on the chi-square test comparison of the food intolerance rate during NICU between groups. Our previous pilot study shows that the rate of food intolerance during NICU for control patients is about 85 %. We expect that the intervention group will have a reduced intolerance rate to be 75 %. With these assumptions, we will need 148 infants in each group to finish the NICU part of the study to reach 80 % power and 5 % Type I error rate. Assuming that the dropout rate to be 20 %, we will need to enroll 185 infants in each group.

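### Four events that can only follow randomisation are listed as exclusion criteria; on the natural reading, severe NEC and infants likely to be intolerant leave the comparison

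*Protocol article*

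**What the plan says.** All references are to the protocol article.

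- **Exclusion criteria (Recruitment of participants).** Several items are tied to the time before enteral feeding is prepared. Others are not. One reads "Occurrence of stage III necrotizing enterocolitis during hospital stay requiring transfer" to a children's hospital. Three more are a change of formula during the stay, death during the stay, and leaving the NICU early against the discharge criteria. Two further items carry no date: use of motility or gastric-acid drugs, and diseases that need parenteral nutrition or serious illness.
- **Allocation (Randomization and blinding).** "The participants who meet the eligibility criteria will be divided into two groups by the physicians on duty via opening the envelopes". Of blinding, the section says that "only the participants and their guardians are unaware of the milk type".
- **Feeding start (Stage I: NICU stay).** Feeding begins within 24 hours of birth, or at 24–72 hours in high-risk infants. To be included, infants must have had no enteral feeding before or during transfer.
- **Endpoints (Outcomes).** "The first endpoint variable is the rate of food intolerance in preterm children". In addition, "Other endpoint variables include the incidences of neonatal necrotizing enterocolitis, cholestasis, parenteral nutrition-associated cholestasis and congenital hypothyroidism". No NEC stage is left out. Growth in the NICU and for 3 months after discharge is a secondary endpoint.
- **Sample size justification.** "we will need 148 infants in each group to finish the NICU part of the study", with 185 enrolled per group to allow for 20% dropout.
- **Statistical analysis.** No analysis population is named.

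**The concern.** An exclusion criterion is harmless to a randomised comparison when it is settled before allocation, or when the assigned treatment cannot influence it. The four events meet neither condition. Each follows exposure to the assigned formula, and each may be a consequence of it. Physicians and nurses who can tell the formulae apart take part in at least the decision to change formula.

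If such infants are removed, the analysis compares those who got through the NICU stay on their assigned formula, not the groups that were randomised. Severe NEC would be both part of an endpoint and a reason for leaving the data set. A formula that produced more severe NEC or more formula changes could look better on the primary endpoint because of those events. The Discussion expects the results to confirm that the formula is safe and works. A data set built in this way could not support that conclusion.

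**Working it through.** **1. Timing.** Infants arrive unfed, are allocated by envelope once eligible, and then receive the allocated formula. Stage III NEC during the stay, formula change and in-hospital death are placed by the list itself, or by their nature, in the hospital stay. Early discharge can only be known when the infant leaves. None of the four can be known when the envelope is opened.

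**2. Overlap with endpoints.** Table 3 sends both stage IIIA and stage IIIB to the children's hospital, so the NEC exclusion covers all of stage III. NEC incidence is an endpoint without a stage limit. NEC is managed by absolute fasting, and needing to fast for more than two meals is one of the six intolerance criteria. An infant with NEC would therefore normally count as intolerant as well.

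**3. The plan's own figure.** 148 / (1 − 0.20) = 185, so the dropout step reproduces, and 185 − 148 = 37 per arm may go unanalysed. The 148 itself does not reproduce: (1.96 + 0.8416)² × (0.85×0.15 + 0.75×0.25) / 0.10² gives 248 per group (250 with pooled variance). That is a separate problem, and nothing here rests on it.

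**4. Size of distortion.** The article gives no removal rates, so the shares below are assumptions. If a share *e* of an arm is removed and all those removed had intolerance, a true rate *p* becomes

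(p − e) / (1 − e).

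*No true effect, 85% in both arms:*
- 20% removed, all intolerant: (0.85 − 0.20)/0.80 = 81.25%. With a random 20% removed from the other arm, that arm stays at 85.0%. The false difference is 3.75 points.
- The same with 10% removed: (0.85 − 0.10)/0.90 = 83.3% versus 85.0%, or 1.7 points.
- Intolerant infants removed from both arms, 10% versus 20%: 83.3% versus 81.25%, or 2.1 points. Two-sided type I error is about 7.8%.
- 0% versus 20%: 85.0% versus 81.25%, with 185 and 148 analysed. The null standard error is √[0.8333×0.1667×(1/185 + 1/148)] = 0.0411 and the actual one is √(0.1275/185 + 0.1523/148) = 0.0415. The upper-tail limit is (1.96×0.0411 − 0.0375)/0.0415 ≈ 1.04. Adding the small lower tail gives a type I error of about 15%.
- Equal shares removed: no false difference, and type I error stays at 5%.

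*Planned effect, 85% versus 75%:*
- Equal 20% removal: (0.85 − 0.20)/0.80 = 81.25% versus (0.75 − 0.20)/0.80 = 68.75%. The true 10 points become 12.5.
- Equal 10% removal: 83.3% versus 72.2%, or 11.1 points.

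**The case against.** The strongest reply is that the article never says that these infants leave the analysis. The list may merge entry criteria with reasons for stopping the study feed. An analysis plan that is not shown could define the population, and the flowchart is not available. The data collection section records the incidence and outcome of intolerance and NEC, and Table 3 retains stages IIIA and IIIB. This stands to the extent that removal is an inference. It is a strong one, because the events are called exclusion criteria, the sample size is built on infants who complete the NICU stage, and nothing in the analysis text restores the rest. An analysis plan that kept these infants would have to override the published criteria.

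A reader might infer more than the text supports:

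- *That severe NEC and death are zero by rule.* This holds only if removal is confirmed, and death is not a listed endpoint.
- *That the motility and acid-drug item is also a post-randomisation exclusion.* It is undated, so this is possible but not shown.
- *That the parenteral-nutrition item excludes everyone, or excludes infants for having the primary event.* The Stage I section does say that "when the children experience feeding intolerance and necrotizing enterocolitis and need to be fasting, complete parenteral nutrition is given", and it gives partial parenteral nutrition until full feeds. But the item speaks of diseases and serious illness, mentions hospitalisation of infants who are already inpatients, and comes last in the list. It may mean illness or readmission during follow-up. The wording is unclear and should be reconciled with Stage I; it is not proof of removal.
- *That the 20% dropout consists of these infants.* The article does not say what it contains.
- *That the bias favours the hydrolysed formula.* It could go either way. For example, infants taken home early may be those who tolerated feeds.

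**Conclusion.** The point holds for the four events. As written, the criteria prescribe exclusion for consequences that may flow from the feeding under test, and on the natural reading the analysed groups are no longer the randomised groups. The NEC endpoint would lose its severe stage, and the primary comparison would lose infants likely to be intolerant.

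Neither the size nor the direction of the bias can be derived from the article. The 3.75-point figure is an extreme case: it takes the whole 20% dropout allowance as removals, all intolerant in one arm and random in the other. Against a planned 10-point effect it would be material. Smaller or more balanced removals would do less, and equal removal of intolerant infants does not create an effect where there is none, though it exaggerates a real one. The two undated criteria need clarifying but do not carry the finding.

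**What to change.** 1. Apply exclusion criteria only to conditions present or known before the envelope is opened. Congenital malformations and metabolic or chromosomal disease found later may remain, because the formula cannot cause them.
2. Analyse all other randomised infants in their assigned arm.
3. For the primary endpoint, count intolerance observed up to transfer, formula change, early discharge or death.
4. Count stage III NEC in the NEC endpoint. Report deaths, formula changes and early discharges by arm.
5. Use growth data up to the event. Later growth of infants who die remains unobservable, so deaths by arm should be shown beside the growth results.
6. Give the motility and acid-drug item and the parenteral-nutrition item a time limit, and reconcile the latter with the Stage I section, where parenteral nutrition is routine until full feeds.

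The cost is protocol wording and an analysis-set definition. Daily intake, gastric residuals, vomiting, distension and NEC are already recorded during the NICU stay, so the data up to each event exist. The downside is that the reported intolerance rates may be slightly less favourable.

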#### Randomization and blinding

Randomization will be conducted by a researcher not involved in the recruitment and treatment of the participants. Concealed allocation will be performed using a set of random numbers placed in sealed opaque envelopes. The participants who meet the eligibility criteria will be divided into two groups by the physicians on duty via opening the envelopes. Reference to similar study literature is made for randomization [28, 31]. As extensively hydrolyzed milk protein formula and preterm children’s formula are greatly different in color and smell, physicians and nurses can easily distinguish these two formulae. Therefore, the study has chosen single-blinding, which means that only the participants and their guardians are unaware of the milk type.

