#### Interventions

The observation group is fed with extensively hydrolyzed milk protein (100 % whey protein) formula, while the control group is fed with preterm children’s formula until discharge from the NICU. After discharge, both groups are uniformly fed with ordinary formula (formula for 0 to 6-month-old infants).

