### Stage II: follow-up period after discharge from the NICU

Develop a follow-up observation table for preterm children <34 weeks, and require the children’s health care medical staff to record the data of follow-up every time in detail.Require the preterm children to revisit the hospital’s Child Health Clinic for referral 2 weeks, 4 weeks and 3 months after discharge, and follow up once every 2–4 weeks according to the preterm children’s conditions 4 weeks later.Call the children’s parents 1–2 day before every referral and require them to bring the children to our hospital for referral on time, and ask them to bring all medical data.Contents of referral at the Child Health Clinic include measurement of physical growth and development, assessment of neuropsychological development, nutritional assessment and feeding guidance. According to different conditions of the preterm children during hospital stay, choose whether to conduct blood, liver function, thyroid function, head B-mode ultrasound or cranial magnetic resonance imaging (MRI), retinopathy (ROP) screening, hearing screening and other tests.Explain the current follow-up results in detail to the parents, and appoint the time and contents of next follow-up.Call the parents again on the night or the next day of follow-up every time to inquire about follow-up conditions in detail, and again record all follow-up results.Follow-up period: at least 3 months.

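### The stated reason for leaving staff unblinded ends at discharge, yet no masked assessor is planned for body length and head circumference at the follow-up clinic

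*Protocol article*

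**What the plan says.** Under Randomization and blinding, the article explains that the hydrolyzed and preterm formulae differ so much in colour and smell that "physicians and nurses can easily distinguish these two formulae". From this it concludes that the trial is single-blind, "which means that only the participants and their guardians are unaware of the milk type". No other reason is given. The Abstract and the opening of Methods/Design also call the trial single-blind, without limiting this to a stage.

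The Interventions section then removes the visible difference at discharge: "After discharge, both groups are uniformly fed with ordinary formula (formula for 0 to 6-month-old infants".

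The Stage II section moves follow-up to the "Child Health Clinic for referral 2 weeks, 4 weeks and 3 months after discharge". It asks the investigators to "require the children’s health care medical staff to record the data of follow-up every time in detail". The visit covers "measurement of physical growth and development, assessment of neuropsychological development, nutritional assessment and feeding guidance". Parents are telephoned beforehand to "require them to bring the children to our hospital for referral on time, and ask them to bring all medical data".

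The section on follow-up data collection lists weight (to 10 g), body length and head circumference (both to 0.1 cm) at the three scheduled visits. Growth within 3 months of discharge is part of the sixth of seven secondary endpoints under Outcomes. The secondary objective includes showing that early growth is unaffected, both in hospital and afterwards.

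**The concern.** A reason for open staff that holds in the NICU is carried over to a stage where it no longer applies. At the clinic there is no study formula to recognise, because every infant is on the same product. An assessor could know the arm only from the records, from the family or from NICU staff, and all three routes can be controlled to some degree.

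What is at stake is the growth comparison after discharge. Table 1 gives the test formula 66 kcal and 1.6 g protein per 100 ml, against 80 kcal and 2.6 g for the preterm formula, so slower growth is an obvious safety question. The hoped-for answer is no effect, and the Discussion says in advance that the results will confirm this. If an assessor knows the arm and leans towards the expected answer, a real deficit can be read as smaller than it is. Length and head circumference are the measurements most exposed, because they depend on how the infant is positioned and where the tape is placed.

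**Working it through.** The plan gives no figure on this point, so nothing can be reproduced. The check sets the sections side by side.

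1. **Reason for open staff.** Visible difference between the two NICU formulae (Randomization and blinding).
2. **Does the reason hold in Stage I?** Yes. NICU staff handle the formula, so NICU growth and feeding intolerance are assessed unblinded for the stated reason. This point does not touch them.
3. **Does the reason hold in Stage II?** No. Both arms take one ordinary formula (Interventions; also the feeding rules under Stage I), so there is nothing to tell apart.
4. **Who assesses in Stage II?** The children's health care staff record the data at the Child Health Clinic. The text describes them separately from the NICU physicians and nurses, but does not say that they have no NICU role.
5. **Is a masked assessor provided anywhere?** No. The word *only* in the blinding statement leaves assessors out of the blind.
6. **Which measurements are exposed?** Length and head circumference, taking these to be measured by hand. Weight, taken to be read from a scale, is little affected.

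**Can the size be estimated?** Suppose an arm-dependent reading shift of 0.2–0.3 cm. Using the Background's ideal rates of 1 cm/week for length and 0.5–1 cm/week for head circumference:

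- Length: 0.2/1 to 0.3/1 = 0.2–0.3 weeks of growth.
- Head: 0.2/1 to 0.3/0.5 = 0.2–0.6 weeks of growth.

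The arithmetic is right, but it does not give an estimate. The shift is an assumption with no source in the document, and the rates are targets for the NICU stay. The form of the analysis also matters. Let *d* be a constant shift at every clinic visit:

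- Growth between two clinic visits: (later + *d*) − (earlier + *d*) = later − earlier, so *d* cancels.
- Growth from the discharge measurement to a clinic visit: (clinic + *d*) − discharge, so *d* stays.

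Over about 13 weeks at 1 cm/week, 0.2–0.3 cm would be 0.2/13 to 0.3/13, or roughly 2% of length gained. The effect thus depends on the interval, on how constant the shift is and on how the repeated-measurement covariance model is set up. None of these can be fixed from the text.

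**The case against.** The strongest reply is that the blinding statement sits with allocation and speaks of the physicians and nurses who see the formulae. It does not mention the clinic. Masking of follow-up assessors and the order of steps at a visit are details that a condensed article may leave to the full protocol. This stands in part: the procedural detail is not owed here. But the article is not silent on who is blind. It says that nobody is except infants and guardians, and it sets no stage limit. That is a stated choice, and its stated reason does not reach Stage II.

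A second reply also stands. Clinic staff give feeding guidance and choose tests according to the infant's course in hospital, so they need the NICU history. Measuring before opening the record protects the first visit, but later visits only if the formula name is absent from the records the same staff consult. The fix must cover this.

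A reader might infer more than the text supports:

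- *That the guardian blind fails at follow-up because parents carry the records.* No section says that these papers name the formula. The request is a possible route, not a demonstrated one.
- *That the measurers are known to be independent of the NICU.* This is a fair reading of the Stage II section, but it is not stated.
- *That post-discharge growth alone carries the safety conclusion.* NICU growth, plasma parameters, necrotizing enterocolitis and cholestasis also contribute.
- *That the bias has a known size.* The working above shows why it has not.

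**Conclusion.** The point holds for Stage II. The only reason given for unblinded staff stops applying at discharge, and the article provides no masking for those who then measure growth. Body length and head circumference at the three scheduled visits are open to avoidable assessor bias in a comparison meant to show no effect on growth. The size of that bias cannot be derived from the document. Nothing shows that it would be large, and the primary endpoint is unaffected.

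The conclusion assumes that length and head circumference are hand measurements, and that clinic assessors can in practice be kept from learning the NICU formula for most infants. It does not require that the parents' papers name the formula or that clinic staff never work in the NICU. The change is worth making because it is cheap and protects a secondary safety comparison, not because the trial fails without it.

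**What to change.** Amend Randomization and blinding to limit the colour-and-smell argument to the NICU stay, and add that the clinic staff who measure growth after discharge are masked to NICU formula and, where possible, took no part in the infant's NICU feeding. To make this work:

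- identify infants by study number, and omit the formula name from the discharge summary, the follow-up table and the hospital records used at the clinic;
- take weight, length and head circumference before the record is reviewed;
- have the NICU team hold the allocation and release it on clinical need.

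Because parents are asked to bring their papers, leaving the formula name off them also protects the guardian blind.

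The cost is wording and the order of steps at visits that already take place, with no added staff, visits or procedures. The small downside is that formula identity must be kept out of routine papers, and masking may fail for some infants.
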